### Statistical analysis

The statistical analysis of this study can be divided into four parts. Firstly, the IBM SPSS Statistics for Windows (Version 26.0 Armonk, NY: IBM Corp) would be used in this study. Data processing was performed to review missing data, followed by screening for normality for all outcome measures and for each treatment group. Secondly, inter-group comparisons were performed prior to the main analysis, and differences between baseline groups were analyzed using Chi-square test and independent sample T-test to verify the success of randomization. If the relevant data did not conform to a normal distribution, the generalized estimation equation (GEE) would be used for analysis. In addition, a preliminary analysis would be performed on an intention-to-treat basis using Generalized linear mixed model (GLMM) to investigate the differential effects of each treatment condition. For the post-treatment analysis in the three treatment conditions, the analysis will focus on the linear time effect, treatment conditions and interaction. Finally, a linear mixed model repeated measures (MMRM) was used to study inter-group differences with primary and secondary outcome measures as dependent variables. The model would include processing conditions and time as classification variables, as well as their interaction effects. The baseline adjusted mean difference between groups at each time point would be calculated using a 95% confidence interval, with the value of alpha set at 0.05. The analysis would focus on the estimated mean differences between primary and secondary outcome indicators at different time points.

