### Study design

This study is a randomized, single-blind, wait-list controlled, parallel-arm trial. Older stroke survivors will be selected from a tertiary hospital in China using convenience sampling between December 2022 to March 2023. Older stroke survivors who meet the inclusion criteria will be informed of the purpose and methods of the study and sign the informed consent forms through face-to-face communication. Then, they will be randomly assigned to either a wait-list control group (TAU group) or an intervention group (group-based ACT group). EA, PSD, psychological distress and quality of life of patients will be blindly evaluated at baseline (T0), post-treatment (T1), one-month follow up (T2) for both groups (see Fig. 1).

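### The analysis section names three conditions in a two-arm trial, treats time as both linear and categorical, only partly ranks its models, and does not say how baseline enters

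*Protocol article*

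**What the plan says.** All of the analysis wording is in one paragraph of the protocol article, under Statistical analysis.

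- **Conditions and time, first statement:** "For the post-treatment analysis in the three treatment conditions, the analysis will focus on the linear time effect, treatment conditions and interaction".
- **Conditional model:** after the sentence on baseline comparisons, "If the relevant data did not conform to a normal distribution, the generalized estimation equation (GEE) would be used for analysis".
- **Preliminary model:** the generalized linear mixed model (GLMM) is introduced as preliminary. It is the only model tied to intention-to-treat.
- **Final model:** "a linear mixed model repeated measures (MMRM) was used to study inter-group differences with primary and secondary outcome measures as dependent variables".
- **Terms of that model:** "The model would include processing conditions and time as classification variables, as well as their interaction effects".
- **Estimate promised from it:** "The baseline adjusted mean difference between groups at each time point would be calculated using a 95% confidence interval", with alpha at 0.05.

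The Study design section gives two arms, a wait-list (usual care) group and a group-based ACT group. Outcomes "will be blindly evaluated at baseline (T0), post-treatment (T1), one-month follow up (T2) for both groups". The Randomization section splits 66 random numbers into 33 and 33. AAQ-II is the primary outcome.

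**The concern.** Four features of the paragraph do not fit the design or each other.

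1. There is no third treatment condition. The word cannot refer to the three assessments, because the same sentence lists time separately.
2. A linear time effect and a categorical one are different models for three assessments. They give different treatment effects unless the group difference really grows in a straight line.
3. Three model families are named. No sentence says which one, or which time point, decides the AAQ-II hypothesis.
4. The MMRM has no baseline term, yet a baseline-adjusted difference is promised at every time point. At T0 that quantity has no meaning.

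Two things are at stake. The choice of model and time point stays open until the data have been seen. And, depending on how baseline is handled, precision may be lost in a trial of 66 patients.

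**Working it through.** The plan states no figure on this point that could be reproduced. The check sets the statements against the design, then works out what each listed model estimates.

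**Step 1. Number of conditions.** Study design and Randomization: 2 arms, 33 + 33 = 66. Statistical analysis: 3 conditions. These contradict each other.

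**Step 2. Linear against categorical time.** Assume a true group difference of 0 at T0, d at T1 and d at T2. A least-squares line is fitted to these three values.

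- Visit number 0, 1, 2: intercept 0.167d, slope 0.5d per visit. Fitted values are 0.17d at T0, 0.67d at T1 and 1.17d at T2.
- Weeks 0, 8, 12 (eight weekly sessions, then about four weeks to T2): intercept 0.071d, slope 0.0893d per week. Fitted values are 0.07d, 0.79d and 1.14d.
- Categorical time: 0, d, d.

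On this course the line understates T1 by 21% to 33% and overstates T2 by 14% to 17%.

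**Step 3. What the listed MMRM terms estimate.** The terms are condition, categorical time and their interaction, with T0 as one of the responses. A simulation used 4,000 runs, 33 per arm and complete data. Its assumed values, not taken from the documents, were SD 1, correlation 0.5 between assessments, and a true effect of 0.5 at T1 and T2.

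| T1 contrast | Mean | SE | Correlation with chance baseline imbalance |
|---|---|---|---|
| Plain difference at T1 | 0.498 | 0.250 | +0.52 |
| Interaction (difference in change from baseline) | 0.503 | 0.244 | −0.49 |
| Baseline score as covariate | 0.501 | 0.215 | 0.03 |

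All three are centred on the true 0.5. Only the covariate removes the dependence on baseline imbalance, and that term is not in the listed model.

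**Step 4. Precision of the two ways of using baseline.** With equal variances and correlation r between baseline and follow-up, the variance relative to an unadjusted difference is 2(1 − r) for a change score and 1 − r² for a covariate. Their ratio is (1 − r²) / [2(1 − r)] = (1 + r)/2, which never exceeds 1. Apart from the one degree of freedom spent, the covariate is therefore at least as precise.

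For illustration, take the HAMD inputs from Sample size calculation: difference 8.9 − 6.5 = 2.4; pooled SD √[(4.0² + 2.9²)/2] = 3.49; d = 2.4/3.49 = 0.687. With 33 completers per arm, two-sided alpha 0.05 and assumed r, noncentral-t power is:

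| r (assumed) | Change score | Baseline covariate |
|---|---|---|
| 0.3 | 64% | 82% |
| 0.5 | 78% | 89% |
| 0.7 | 94% | 97% |

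An unadjusted comparison of follow-up scores has 78% on the same inputs.

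**The case against.** **The models are not equal rivals.** A reader might infer three competing p-values for one hypothesis. The paragraph does not support that. The GLMM is called preliminary, the MMRM comes last and is the only model explicitly tied to the primary and secondary outcomes, and GEE is conditional. This stands. What remains is an unfinished ranking: no model is called primary and no time point is named.

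**The MMRM can use baseline.** It is tempting to say that none of the listed models can give a baseline-adjusted difference. That goes too far. With T0 among the responses, the interaction contrast is a difference in change from baseline, and a constraint of equal baseline means would give a fully adjusted difference. The defect is that the listed terms contain no baseline covariate and the text does not say which adjustment is meant.

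**The scope of the GEE sentence is unclear.** It follows the baseline tests directly, so one cannot assert that GEE replaces the MMRM. But the normality screen covers all outcome measures by group and GEE is a repeated-measures method, so that reading is open and should be closed. Nor does the plan forecast 30% loss: it expands 25 per group to 33, which covers 8/33 = 24%.

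**The linear-time figures depend on an assumed course.** No section says that the effect is complete at T1 and held at T2. The wait-list group is to receive ACT once the intervention group has finished, which makes a held difference less secure. If the post-treatment analysis uses only T1 and T2, a line through two points fits exactly and the distortion disappears. This stands, so the figures are conditional. The conflict between the two statements about time does not depend on them.

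**The power figures are not this trial's primary power.** They use a HAMD effect, a secondary outcome here, because no AAQ-II effect is given. They also assume r and no loss. With 25 completers per arm the same inputs give 66% unadjusted and 78% with a covariate at r = 0.5. The figures show the direction and rough size of the gain, no more.

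**Conclusion.** The point holds in limited form. It needs no outside assumption to say that the paragraph contradicts the two-arm design, describes time in two incompatible ways, leaves the deciding model and time point for AAQ-II unnamed, and promises a baseline-adjusted difference without saying how baseline enters.

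The sizes are conditional. The 0.67 to 0.79 at T1 and 1.14 to 1.17 at T2 need T0 in the fit and an effect complete at T1 and held. The advantage of a covariate over a change score (82/89/97% against 64/78/94% power) needs the HAMD effect size, 33 completers per arm and r of 0.3, 0.5 and 0.7.

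This should be corrected before analysis. It does not show that the MMRM is unsuitable; suitably specified, it is the natural primary analysis.

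**What to change.** Rewrite the paragraph as follows.

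- Change three treatment conditions to two, and drop the focus on a linear time effect.
- Make the MMRM the single primary analysis, in all randomised patients, with T1 and T2 scores as responses. Terms: arm, categorical visit, arm × visit, baseline score of that outcome, and baseline × visit.
- Name one primary time point for AAQ-II, and report adjusted differences with 95% confidence intervals at T1 and T2 only.
- Do not let a normality screen of raw scores select the model, because the MMRM's assumption concerns residuals. Check residuals, and label any GEE or resampling analysis as sensitivity only.

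Covariance structure and the degrees-of-freedom method can be left to the statistical analysis plan. The cost is one rewritten paragraph, with the assessments already scheduled and no change to recruitment.

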The Canadian Stroke Best Practice Recommendations, CSBPR) state that psychotherapy, including cognitive behavioral therapy, is one of the most commonly used strategies for post-stroke depression [16]. Acceptance and commitment therapy (ACT), referred to as the third wave of CBT, is a kind of behavioral therapy based on functional contextualism and relational framing theory [20]. The core component and the ultimate goal of ACT theory is to improve the individual’s psychological flexibility [21], that is, to fully feel, perceive and accept the things and emotions you experience at the moment, rather than focusing on avoiding painful memories or negative emotions in reality, and to make behavioral changes according to the direction of their own values, so as to change the relationship between cognition and emotion. ACT has been increasingly used in the psychological aspect of stroke survivors [5, 22, 23]. It can effectively relieve the psychological distress of stroke survivors and improve their quality of life, which may be related to ACT’s ability to reduce patients’ EA and improve their psychological flexibility.

In groups, people can socialize with peers with similar symptoms, have the opportunity to improve one’s altruism and empathy, and feel useful by helping others. In addition, group therapy results in a more cost-effective professional/client ratio [24]. In particular, group therapy provides an opportunity for depressed older adults, who often live in isolation and have lost significant relationships, capacities, or occupations, to once again feel connected with and useful to the society, as well as to (re)discover their meaning in life. Therefore, group-based ACT may have more unique therapeutic benefits, such as reducing feelings of isolation, providing opportunities to learn from the experience of other attendees, and developing new coping strategies and behavioral patterns based on such shared learning for older stroke survivors in China.

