### Intervention group

All interventions received by the intervention group were carried out in a separate activity room with an area of 20 m^3^ to ensure no interference. The activity room will be equipped with seats approximately, drinking water, and other necessary items. Moreover, necessary first-aid items will be also provided to ensure patient safety. The research team will provide materials and related things for ACT. Throughout the intervention, the health care workers will keep the patient safe at all times.

For the intervention group, group-based acceptance and commitment therapy intervention will be given for 8 weeks in addition to TAU, which will be completed by 2 graduate students, both of whom were systematically trained group-based ACT consultants, and will also lead the group consultation activities. Each group-based ACT intervention will consist of 10 ~ 12 people, once a week for 40 to 60 min, for 8 consecutive weeks. The content consists of eight sessions: confronting the agenda, accepting everything, objectively observing cognition, the hours, feeling yourself, identifying your value, looking forward, and review. The specific intervention content of each module is shown in Table 1.

**Table 1 Tab1:** An overview of the group-based ACT program for older stroke survivors

Session	Content
Confronting the Agenda	Start with an “Ice-breaking tour” (5–10 min) Patient self-introduction (10–15 min) Introduction of ACT team members and content (5 min) Mindfulness exercises (10–15 min) Home task (5 min)
Accepting everything (Acceptance)	Begin with a mindfulness exercise and homework review (5–10 min); Watch a video of sinking into a swamp (10-15 min); Play the game “Chinese Finger Glove” (10–15 min); Share and summarize (10–15 min); Home task (5 min).
Observing cognition objectively (Cognitive Defusion)	Homework review (5–10 min); Play the video “Passengers on the Bus” (5–10 min); Play the game “Folder push” (10 to 15 min); Share and summarize (10–15 min); Home task (5 min).
The Hours (Being Present)	Begin with a review of last week’s homework (5-10 min); Mindful eating (10 min); Mindful breathing exercise (10-15 min); Share and summarize this activity (5–10 min); Home task (5 min).

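### Neither the stated models nor the sample size account for the ACT therapy groups, so any positive within-group correlation makes the intervals too narrow and the type I error exceed 5%

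*Protocol article*

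**What the plan says.** The Intervention group section of the Protocol article sets the unit of delivery: "Each group-based ACT intervention will consist of 10 ~ 12 people", meeting weekly for eight weeks. Delivery is by two people ("which will be completed by 2 graduate students"). The Introduction gives a reason for choosing groups, namely that members learn from one another: "developing new coping strategies and behavioral patterns based on such shared learning". The session table schedules sharing between members in most weeks.

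The Statistical analysis section names three kinds of model:

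- For the MMRM: "The model would include processing conditions and time as classification variables, as well as their interaction effects".
- For the preliminary GLMM: "the analysis will focus on the linear time effect, treatment conditions and interaction".
- For non-normal data: "the generalized estimation equation (GEE) would be used for analysis", with no clustering unit given.

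A 95% interval is to be reported at each time point, "with the value of alpha set at 0.05". Therapy group is not mentioned for any of these models. The Sample size calculation section uses the formula for two independent means, with 25 per group raised by 30% to 33 per group.

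**The concern.** Patients who sit in the same ACT group share sessions and peers for eight weeks. If they influence each other, as the rationale hopes, their outcomes are correlated. The mean of the ACT arm then varies more than 33 independent patients would make it vary. The control arm is not described as being treated in fixed groups, so the design is partially nested: clustered in one arm and unclustered in the other.

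Modelling repeated measures deals with correlation within a patient over time. It does nothing about correlation between patients in one therapy group. If group is left out, the standard error of the difference between arms is too small, and the chance course of one of about three groups can be taken for a treatment effect. The interval and the alpha of 0.05 would then not have the properties claimed for them.

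**Working it through.** **The plan's own figure.** From the HAMD values 8.9 (SD 4.0) and 6.5 (SD 2.9), delta = 2.4, pooled SD = sqrt((16 + 8.41)/2) = 3.494, and d = 2.4/3.494 = 0.687. The printed formula gives 2 × (3.24/0.687)² + 1.96²/4 = 45.5, so 46 per group and not the stated 25. The step 25 × 1.3 = 32.5, rounded to 33, does reproduce. The mismatch in the 25 is a separate error, and nothing below depends on it.

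**Number of groups.** 33/12 = 2.75 and 33/10 = 3.3, so about three groups, taken here as 3 groups of m = 11.

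**ICC.** The documents give none for therapy group; the coefficient called ICC in the HAM-D section is retest reliability. A range is therefore assumed.

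**Formulas.** With clustering in the ACT arm only and equal arms:

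- ACT-arm design effect: D = 1 + (m − 1) × ICC
- True SE / naive SE: R = sqrt((1 + D)/2)
- Type I error of a nominal 5% test: 2 × [1 − Φ(1.96/R)]
- Power at n = 33 with clustering counted: Φ(d / sqrt((1 + D)/33) − 1.96)

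| ICC | D | R | Type I error | Simulated | Power |
|---|---|---|---|---|---|
| 0 | 1.0 | 1.000 | 5.0% | 4.9% | 79.7% |
| 0.01 | 1.1 | 1.025 | 5.6% | 5.7% | 77.7% |
| 0.02 | 1.2 | 1.049 | 6.2% | 6.2% | 75.8% |
| 0.05 | 1.5 | 1.118 | 8.0% | 8.1% | 70.4% |
| 0.10 | 2.0 | 1.225 | 11.0% | 11.1% | 62.5% |

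Example at ICC 0.05: D = 1 + 10 × 0.05 = 1.5; R = sqrt(2.5/2) = 1.118; 1.96/1.118 = 1.753; two-sided tail 8.0%.

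The simulated column is an unclustered t-test on 3 × 11 ACT patients and 33 controls (200,000 runs). A baseline-adjusted ANCOVA that ignores group gave 8.0% and 11.0% at ICC 0.05 and 0.10 (40,000 runs), so adjusting for baseline does not remove the inflation when the ICC is that of the residuals.

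**Sensitivity to group size.** At ICC 0.05, m = 10 gives 7.7% and m = 12 gives 8.3%. If only 25 per arm are analysed, m averages 25/3 = 8.33:

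- ICC 0.05: D = 1.367, R = 1.088, type I error 7.2%.
- ICC 0.10: D = 1.733, R = 1.169, type I error 9.4%.

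**Sample size.** With n per arm = (1 + D) × (3.494 × 3.2416/2.4)² and 90% power, the number before dropout is 45 at ICC 0, 49 at 0.02, 56 at 0.05 and 67 at 0.10.

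**How well three groups support an adjusted analysis.** A comparison of ACT group means with controls, using Satterthwaite degrees of freedom, had simulated type I error of 5.5% to 6.9% for ICC 0 to 0.20. Its power was about 55% at ICC 0.05.

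**The case against.** The strongest reply is that the article does not say that patients are treated as independent. The MMRM sentence lists classification variables. It names no patient-level covariance, which an MMRM must have, and the baseline adjustment appears only in the next sentence, so the list is not exhaustive. GLMM random effects and the GEE clustering unit are not given, and such detail may sit in an analysis plan that is not shown. This stands. A reader might infer that every planned model ignores grouping and that the type I error certainly exceeds 5%. The article supports less: no model is stated to account for group, and the inflation is conditional on a positive ICC. The reply does not cover the sample size, which is given in full with no design effect.

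Other limits also stand:

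- **Leaders and WeChat.** The article does not divide the two leaders between groups, and it speaks of a single WeChat group that may serve the whole arm. Neither clearly creates differences between groups; shared sessions and peers do.
- **Controls.** That they are ungrouped before T1 is inferred. The Wait-list control group section mentions a separate room but not whether TAU is individual or collective.
- **Power.** The figures concern HAMD, a secondary outcome, because the sample size was based on it. They do not describe power for the primary AAQ-II. They are normal approximations, and they take no account of the few degrees of freedom that three groups leave.
- **T2.** The Wait-list control group section gives controls ACT once the intervention group has finished, so treating each control as unclustered is safe only at T1.

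**Conclusion.** The concern holds conditionally. The plan delivers treatment in about three groups, bases part of its rationale on members affecting one another, and neither states a model that accounts for group nor allows for it in the sample size. With any positive therapy-group ICC, the 95% interval and the alpha of 0.05 are too optimistic. The effect is small at ICC 0.01 to 0.02 and material at 0.05 to 0.10, where the true standard error is 12% to 22% larger than the naive one.

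These sizes assume equal groups, ungrouped controls and an ICC range that is not from the documents. The direction needs only a positive ICC. The point should be acted on, but it does not by itself invalidate the trial.

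**What to change.** 1. Record each ACT patient's therapy group in the data set.
2. For the T1 comparison, fit a partially nested model: a random therapy-group effect in the ACT arm only, each control as a singleton, and Satterthwaite or Kenward-Roger degrees of freedom.
3. Because three groups estimate the ICC poorly, also report the T1 interval with the ACT-arm variance multiplied by 1 + (m − 1) × ICC, with m the mean group size analysed, for fixed ICCs from 0.01 to 0.10. These intervals should carry most of the weight in interpretation.
4. At T2, code the controls' own ACT groups if they have started ACT by then.

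The practical cost is one recorded variable and a short addition to the analysis code. The statistical cost is a wider, less favourable interval (2.5% wider at ICC 0.01, 22.5% wider at ICC 0.10, with 3 groups of 11) and lower power, which no analysis of three groups can restore.

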### Primary outcome measures

#### The Acceptance and Action Questionnaire-II, AAQ-II

AAQ-II scale, a seven-item questionnaire developed by Bond et al. [28] in 2011, was used to assess EA. In the questionnaire, items are scored on a 7-point Likert scale with a total score ranging from 0 to 49, and a higher score indicating more EA. The internal consistency of the AAQ-II is good (Cronbach α = 0.84) [28]. In 2013, Yao et al. [29] measured the reliability of Chinese version of Acceptance and Action Questionnaire-II (AAQ-II), which consists of 10 items rated on a Likert scale of 1 ~ 7 points. The score for items 2 ~ 5 and 7 ~ 9 is reversed. The total possible score ranges from 10 to 70, with higher scores representing higher levels of general acceptance. The coefficient of Cronbach’s α for the Chinese version was 0.705, and the standardized item alpha was 0.758, indicating a good internal consistency of the questionnaire.

